### **9.5.2 Secondary variables**

The secondary variables are:

- Sociodemographic, medication and disease characteristics including RA disease activity scores of DAS28, CDAI/SDAI and proportion of patients with high or moderate disease activity as per DAS28, CDAI/ SDAI.
- Proportion of patients in which treating physician is going to switch the DMARD therapy. Proportion of different mode of action of next planned DMARD.
- Effectiveness, Side effects, Convenience, Global Satisfaction sub scores of TSQM 1.4.
- Total fatigue score measured by FACIT-F.
- RA functional capacity score of HAQ-DI.
- Duration and severity of morning stiffness scores.
- Worst reported pain score.
- Self-reported adherence score (VAS).
- Total score and individual components of WPAI-RA score (% Presenteeism, % Absenteeism, % Total work productivity impairment, % Total activity impairment).
- General quality of life Total score, PCS-score and MCS-score domains and scale scores of SF-36v2 for the full study population.
- Total Electronic health literacy scale score as measured by eHEALS for the full study population.

- Health resource utilization assessment scores in 12 months preceding the study inclusion for the full study population.
- Proportion of patients with different level of patients' need of PSP support for each question point as measured by AbbVie developed questionnaire
- Proportion of patients for each question point about patients' medication preferences as measured by AbbVie developed questionnaire
- Proportion of patients with different level of patients' treatment expectations for each question point as measured by AbbVie developed questionnaire

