#### Comparative subgroup analysis

Subgroup analyses of all measures listed above are planned if there are sufficient patients in each subgroup listed below:

- According to the RA treatment
  - Patients currently treated with any synthetic DMARDs, tsDMARDs, csDMARDs, bDMARDs

- Patients with previous exposure to 1 bDMARD or 2 bDMARD
- Patients treated with orally or parenterally administered DMARD
- Patients treated with IV or SC administered DMARD
- Patients treated with DMARD monotherapy or combination therapy
- According disease activity (high or moderate)
- According to comorbidities
  - Patients with or without any kind of comorbidity
  - Patients with cardiovascular comorbidity

For continuous variables two sample t-tests or non-parametric tests will be used based on the data distribution; for categorical variables appropriate R×C tables will be constructed and Chi-square or exact Fisher tests will be used based on appropriate assumption.

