### Appendix 3: Questionnaire to assess patient needs for support via PSP

This survey asks your needs related a patient support program\* (PSP) for your RA. Please see the short description of PSP in the end of the survey.

For each questions, please cselect one ansver which reflect your needs most likely.

Please use a scale of 1 to 7 where 1 is 'Not needed at all', 4 is 'Unsure' and 7 is 'Very much needed'

|                                                                                           | 1                         | 2 | 3 | 4      | 5 | 6 | 7                        |
|-------------------------------------------------------------------------------------------|----------------------------------|----------|----------|---------------|----------|----------|---------------------------------|
|                                                                                           | Not
needed
at all |          |          | Unsure |          |          | Very
much
needed |
| Do you need a Patient Support Program in general?                                  | 1                                | 2        | 3        | 4             | 5        | 6        | 7                               |
| Do you need a Call center/Hotline?                                                 | 1                                | 2        | 3        | 4             | 5        | 6        | 7                               |
| Do you need Educational materials about RA disease?                                | 1                                | 2        | 3        | 4             | 5        | 6        | 7                               |
| Do you need Educational materials about the therapy you take for RA?               | 1                                | 2        | 3        | 4             | 5        | 6        | 7                               |
| Do you need Nursing service?                                                       | 1                                | 2        | 3        | 4             | 5        | 6        | 7                               |
| Do you need personalized Care coach?                                               | 1                                | 2        | 3        | 4             | 5        | 6        | 7                               |

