## Appendix 5: Questionnaire to assess treatment expectations

Please take some time to think about the key areas of your health related to RA in which you would like to see improvement.

Please use a scale of 1 to 7 where 1 is 'No improvement needed', 4 is 'Some improvement needed', and 7 is 'The most improvement needed'

|                                               | 1                             |          |          | 4                               |          |          | 7                                   |
|-----------------------------------------------|--------------------------------------|----------|----------|----------------------------------------|----------|----------|--------------------------------------------|
|                                               | No
improvement
needed | 2 | 3 | Some
improvement
needed | 5 | 6 | The most
improvement
needed |
| General improvement of arthritis              | 1                                    | 2        | 3        | 4                                      | 5        | 6        | 7                                          |
| Less joint pain                               | 1                                    | 2        | 3        | 4                                      | 5        | 6        | 7                                          |
| Less joint swelling                           | 1                                    | 2        | 3        | 4                                      | 5        | 6        | 7                                          |
| Lasting relief of RA symptoms                 | 1                                    | 2        | 3        | 4                                      | 5        | 6        | 7                                          |
| More joint flexibility                        | 1                                    | 2        | 3        | 4                                      | 5        | 6        | 7                                          |
| Improvement in morning stiffness in the limbs | 1                                    | 2        | 3        | 4                                      | 5        | 6        | 7                                          |

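### The 28 ordered 1–7 items on support needs and treatment expectations are most naturally routed to unordered chi-square or Fisher tests in the subgroup comparisons; an ordinal comparison with an effect estimate would be a cheap, minor improvement

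*Protocol*

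**What the plan says.** Appendix 3 (needs for a patient support program) has 17 items and states "Please use a scale of 1 to 7 where 1 is 'Not needed at all', 4 is 'Unsure' and 7 is 'Very much needed". Appendix 5 (treatment expectations) has 11 items and states "Please use a scale of 1 to 7 where 1 is 'No improvement needed', 4 is 'Some improvement needed", with 7 as the greatest need for improvement. All 28 items are ordered.

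Section 9.5.2 defines the matching secondary variables as "Proportion of patients with different level of patients' need of PSP support for each question point" and "Proportion of patients with different level of patients' treatment expectations for each question point".

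Section 9.5.3 then works with two classes of variable:

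- Under descriptive statistics, categorical variables get counts, proportions and a CI for the proportion. Continuous variables get means, medians and quartiles.
- Under comparative subgroup analysis, which covers all measures, the rule for the first class is "for categorical variables appropriate R×C tables will be constructed and Chi-square or exact Fisher tests will be used". For the second it is "For continuous variables two sample t-tests or non-parametric tests will be used based on the data distribution".

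No class for ordered categories appears and no trend test is named. Rank methods are mentioned only for continuous variables.

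**The concern.** An item summarised by its proportion at each level falls on the categorical side of the two-class rule. Comparing two subgroups on it then means a 2×7 chi-square or Fisher test. That test returns the same answer if the seven levels are shuffled. A general move toward higher ratings is therefore spread over 6 degrees of freedom, where a rank test puts it on 1.

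The secondary objectives in Section 7.2 ask for needs and expectations to be evaluated by treatment, disease activity and comorbidity, and Section 6.2 says the data may inform the design of future support programs. The useful answer is which subgroup rates higher, and by how much. The chi-square test carries no direction, and it is the less sensitive choice when the difference is a shift. At stake is the efficiency and readability of 28 secondary comparisons per subgroup factor.

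**Working it through.** **Inputs from the protocol.** Items: 17 (Appendix 3) + 11 (Appendix 5) = 28, each with 7 ordered levels. Total N about 1500 (Section 9.3). Test for categorical variables: chi-square or Fisher (Section 9.5.3).

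**Assumptions, not in the protocol.** Two-sided 5% level; a one-directional (proportional-odds) shift; odds ratios 1.2 to 1.8; four baseline item shapes (uniform, bell, skewed to high ratings, U-shaped); splits 750/750, 1200/300, 1350/150 and 150/150.

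**The plan's own figures.** Section 9.3 gives precision only for TSQM global satisfaction. With half-width = t(0.975, n−1) × 20/√n, the results are 1.013 (n=1500), 5.684 (n=50), 7.468 (n=30) and 2.789 (n=200), which match the stated 1.01, 5.68, 7.47 and 2.79. No figure is stated for the 28 items.

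**Degrees of freedom.** A 2×7 table has (2−1)×(7−1) = 6. A rank-sum or trend test has 1. For three groups the counts are (3−1)×(7−1) = 12 and 2.

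**Analytic power at equal noncentrality.** Power = P(noncentral χ² with df and λ exceeds the 95th percentile of χ² with df). Critical values are 3.84 (1 df) and 12.59 (6 df).

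| Rank test power (1 df) | λ | Chi-square power (6 df) | Gap, points |
|---|---|---|---|
| 70% | 6.17 | 41.4% | 28.6 |
| 80% | 7.85 | 52.1% | 27.9 |
| 90% | 10.51 | 67.0% | 23.0 |

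- The largest analytic gap is 28.7 points (72.6% against 43.9%).
- For 80% power on 6 df, λ must be 13.62. The ratio 13.62/7.85 = 1.74 is the factor by which the number of patients would have to grow.
- With three groups, where Kruskal-Wallis (2 df) has 80%, the 12-df chi-square has 48.6%.

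**Simulation.** 4000 replicates per setting, Pearson chi-square against tie-corrected Wilcoxon, ranges over the four item shapes:

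| Split | Odds ratio | Wilcoxon | Chi-square | Gap, points |
|---|---|---|---|---|
| 750/750 | 1.3 | 81–83% | 52–55% | 27–29 |
| 1200/300 | 1.4 | 83–85% | 52–59% | 26–30 |
| 1350/150 | 1.5 | 74–77% | 41–48% | 28–34 |
| 150/150 | 1.8 | 80–82% | 51–54% | 27–29 |

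The gap closes when power is already near 100% (0 points at 750/750, odds ratio 1.8). It is also small when power is very low (6–7 points at 150/150, odds ratio 1.2).

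**No difference.** Bell-shaped item, 300/300: both tests reject in 5.7% of replicates. The choice does not affect type I error.

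**A difference that is not a shift.** Level proportions 0.05, 0.10, 0.20, 0.30, 0.20, 0.10, 0.05 against 0.09, 0.11, 0.18, 0.24, 0.18, 0.11, 0.09, 300/300: chi-square 63%, Wilcoxon about 5%. The ranking reverses.

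**The case against.** **The routing is inferred.** The protocol nowhere calls these items categorical, and Section 9.5.2 may be read as no more than a reporting format. If the ratings were treated as scores, the rule for continuous variables would already allow non-parametric tests. This stands in part: the classification is the most natural reading, not an explicit statement. But the two-class rule and the proportion definition point the same way, and the doubt is itself a reason to settle the matter.

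**It is detail for the SAP.** Section 9.5.3 announces a separate SAP, which could name an ordinal method. However, the protocol does not leave this blank. It names tests for the class these items appear to fall in, and those tests suit them poorly.

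**The readout is not blind to direction.** A reader might infer that no one could tell which subgroup needs more support, or that the chi-square p-value is the only comparison planned. The protocol supports neither. Proportions per level with CIs, shown by subgroup, do display direction. Section 9.5.3 also plans crude effect measures, correlations and regressions of needs and expectations on patient characteristics, in the full population and in the subgroups. It names linear models for continuous responses and logistic models for binary ones, and no ordinal model, so those analyses do not close the gap for a seven-level item.

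**Power is a soft yardstick here.** Section 9.7 rules out formal hypothesis testing, reads p-values descriptively and calls subgroup comparisons exploratory. No decision threshold is set for these items. This stands, and it caps the severity.

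**The gain runs one way only.** Under polarised answers chi-square does better. That is plausible for Appendix 3, whose midpoint is labelled as unsure. This stands, and it is why the per-level display must stay.

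**Conclusion.** The point holds as a minor, cheap improvement. As written, the protocol most naturally sends 28 ordered items to a test that ignores their order. For a one-directional shift, that test has about 52% power where a rank test has 80%, and 67% where it has 90%. Simulated gaps are mostly 25 to 30 points where the rank test has about 75 to 85% power, and reach 34 in the most uneven split.

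These sizes rest on an assumed 5% level and assumed odds ratios, splits and item shapes; the protocol supplies none of them. They do not apply to differences that are not a shift.

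The effect is confined to descriptive, exploratory secondary comparisons. A reader might infer that the study's conclusions or error rates are compromised. They are not: the primary endpoint (TSQM 1.4) is not among these items, and both tests hold about 5% under no difference.

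**What to change.** In Section 9.5.3, under comparative subgroup analysis, add wording to this effect: the 1–7 items of Appendices 3 and 5 are ordinal; subgroups are compared with the Wilcoxon rank-sum test (Kruskal-Wallis for more than two groups) or a proportional-odds model, and the result is reported as a common odds ratio, or the probability that a patient in one group rates higher than a patient in the other, with its 95% CI. Keep the proportions per level as the descriptive display, and keep chi-square or Fisher for nominal items such as preferred route of administration in Appendix 4. The same wording could go in the SAP.

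The cost is a sentence or two, with no new data and no more patients. The downside is that a rank test can miss polarising differences that chi-square would pick up. The per-level proportions must therefore be retained and read alongside the effect estimate.

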#### Relationship between variables and predictive models

Relationship analysis is planned between treatment satisfaction and its subdomains; between adherence and its subdomains; between medication preferences, between treatment expectations and between specific PSP-related needs and patient characteristics in the full population and the subgroups specified above. Appropriate data visualization techniques will be used for relationships investigation. Correlation analysis for continuous variables or calculation of crude measure of effect for categorical data can be used if appropriate. Strength of relationships between two variables will be investigated with appropriate univariate regression analysis. Linear regression model will be used for continuous response and predictor variables that satisfy appropriate assumptions of conducting linear regression; logistic regression model will be used for in case of binary dependent variables and continuous or categorical independent variables that satisfy appropriate assumptions.

Predictive models will be constructed using the multivariate linear or logistic regression analyses, as appropriate to data type and regression assumptions. Stepwise selection will be used in defining estimation parameters of the final model. Predictors of switching DMARD therapy will be determined. Patient demographics and clinical characteristics will be considered in the multivariate analysis as predictor variables.

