#### **The following data will be collected:**

1. Demographic data: age, gender, race, occupation, education, place of living (rural/urban)
2. RA disease related data
  - Year of RA diagnosis
  - Diagnostic criteria used for RA diagnosis
  - Current disease activity measured by DAS28 and SDAI/CDAI
  - Imaging results: Presence/absence of structural damage by X-ray (X-ray assessment not older than 6 months from enrollment is acceptable)
  - Laboratory tests: rheumatoid factor (RF) (not older than 3 months from enrollment), anti-citrullinated protein antibody (ACPA) (not older than 3 months from enrollment), current CRP

- Current co-morbidities (including but not restricted to metabolic, cardiovascular, mental, endocrine diseases according latest version of MeDRA)

3. Medication related data

- Prior and current treatment for RA
- Current concomitant medication for comorbidities
- Treatment strategy of treating rheumatologists: whether there is a plan for switching to a different DMARD (Yes / No); in case of plan to switch: mode of action of next DMARD.

4. Health care resource utilization (HRU) in the past 3 months from enrollment.

5. Patient reported outcomes

- Current physical function measured by HAQ-DI
- Level of fatigue measured by FACIT-F
- Duration and severity of morning stiffness measured by VAS
- Level of worst joint pain measured by VAS
- Satisfaction with current treatment for RA measured by TSQM version 1.4
- Self-reported adherence measured by 0-100 mm VAS
- Workability measured by WPAI-RA
- Quality of life health assessment measured by SF-36v2
- Assessments on electronic health literacy by eHEALS
- Questionnaires to assess patient needs for support via PSP, medication preferences and treatment expectations

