### **9.3 Study Size**

Approximately 1500 RA patients will be included in the study. The study will include 100 sites in approximately 20 countries in Europe, America and Asia. Countries will recruit between 30 and 200 patients per country depending on the available patient population.

Current sample size calculation is based on information of global satisfaction measured by TSQM 1.4. It is also assumed that similar number of patients will be allocated to each country so that country level analyses will be explored, as well as overall population. Based on the literature [51, 83], it seems reasonable to assume that the standard deviation for the global satisfaction is about 20 with mean value range from 71 – 91.

A given sample size of N=1500 will be able to provide a 95% confidence interval (CI) with a half width of 1.01 in the overall study population.

For country specific analysis a sample of N=50 will be able to provide a 95% confidence interval (CI) with a half width of 5.68. . For country specific analysis a sample of N=30 – 200 will be able to provide a 95% confidence interval (CI) with a half width of 7.47 to 2.79.

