## **9.7 Limitations of the Research Methods**

Results cannot be generalized to the whole RA patient population universe due to enrolment of sub optimally controlled patients.

Results must be carefully interpreted due to the observational and cross-sectional nature of the study. Information about the percentage of screened patients that agreed to participate in this study will be not collected which may result in selection bias.

No hypothesis testing will be performed in the primary analysis. All other statistical tests performed in secondary analysis will be performed without formal hypothesis testing and resulting p-values will be interpreted in a descriptive manner.

Factors associated to cultural differences may influence the results per countries. Country specific sub analyses should be interpreted carefully due to low sample size.

There is a potential imbalance in the size in subgroups per treatment used or per presence of comorbidities. Comparisons between different subgroups should be interpreted in exploratory manner only. Confounding factors (e.g., disease duration and severity, level of treatment response, and number and type of co-morbidities) may not be equally distributed between the groups, which can lead to bias and subsequent misinterpretation.

No validated questionnaires will be used for assessing needs for PSP, treatment preferences and expectations. Adherence results will be based on self-reported outcomes that may be influenced by self-presentational and recall biases. Patients may overestimate the extent of their adherence. Past HRU is based on patient interviews in addition to patient charts, similarly might result in recall-biases.

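### The pooled regression models, including the model of planned DMARD switch, name patient characteristics as predictors but neither country nor site, so between-country differences may be read as patient effects

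*Protocol*

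**What the plan says.** Protocol section 9.5.3, under the heading on relationships and predictive models, sets out how satisfaction, adherence, medication preferences, treatment expectations and support-programme needs will be related to "patient characteristics in the full population and the subgroups specified above". Pairs of variables are examined by univariate linear or logistic regression. Multivariable models follow: "Stepwise selection will be used in defining estimation parameters of the final model". The section adds: "Predictors of switching DMARD therapy will be determined". The candidate predictors are given in one sentence: "Patient demographics and clinical characteristics will be considered in the multivariate analysis as predictor variables".

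Section 8.1 lists "Demographic data: age, gender, race, occupation, education, place of living (rural/urban" and names neither country nor site there.

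On the sample, section 9.3 says "Approximately 1500 RA patients will be included in the study", from 100 sites in about 20 countries on three continents, and "Countries will recruit between 30 and 200 patients per country depending on the available patient population".

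The protocol recognises variation between countries in three places. Section 9.7 says "Factors associated to cultural differences may influence the results per countries". Section 9.1.1 accepts the ESR form of DAS28 because practice differs between countries. Section 9.2 notes that questionnaire versions may differ by country after translation.

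**The concern.** A pooled regression without country mixes two comparisons: patients within a country, and one country with another. Drug class, route of administration, line of biologic therapy, education, race and rural living may all differ in frequency between countries. Satisfaction scores, reported adherence and expectations may differ between countries too, through culture, translation or care. Where both sides vary by country, part of the between-country difference goes into the coefficient of the patient characteristic.

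The switch outcome is exposed in a further way. It is the treating rheumatologist's plan, and a site contributes 15 patients on average (1500/100). Some of its variation may belong to the physician or site and not to the patient.

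Five secondary objectives in section 7.2 concern relationships with patient characteristics, and a sixth concerns treatment strategy. Section 6.2 hopes that the results will guide personalised treatment and the design of support programmes. A national practice pattern mistaken for a patient trait would misdirect that use.

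**Working it through.** **The plan's own figure.** Section 9.3 gives a 95% half width for mean TSQM global satisfaction, with SD 20. The formula is t(0.975, n−1) × 20/√n:
- n = 1500: 1.9616 × 20/38.730 = 1.013 (stated 1.01)
- n = 50: 5.684 (stated 5.68)
- n = 30 and n = 200: 7.468 and 2.789 (stated 7.47 and 2.79)

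These reproduce, with patients treated as independent. The protocol gives no figure for the regression models, so their size has to be shown over assumptions.

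**Inputs from section 9.3.** N = 1500, 20 countries (mean 75 patients), 100 sites (mean 15), SD 20.

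**Assumptions.** The protocol gives no ICC, no between-country spread of any characteristic, and no correlation between country effects on predictor and outcome.

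**Check 1: continuous predictor, 20 countries of 75.** The true within-country slope is zero, with 1000 runs per row. Slopes are in TSQM points per SD of the predictor.

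| Predictor ICC | Outcome ICC | Correlation of country effects | Rejects, no country | Mean slope, no country | Rejects, with country | Mean slope, with country |
|---|---|---|---|---|---|---|
| 0.05 | 0.05 | 0 | 7.1% | −0.01 | 3.5% | 0.00 |
| 0.10 | 0.10 | 0 | 11.4% | 0.01 | 3.9% | 0.02 |
| 0.20 | 0.10 | 0 | 20.2% | −0.01 | 4.7% | 0.01 |
| 0.05 | 0.05 | 0.5 | 17.2% | 0.47 | 4.9% | 0.00 |
| 0.10 | 0.10 | 0.5 | 45.7% | 0.95 | 5.1% | 0.02 |
| 0.20 | 0.10 | 0.5 | 66.8% | 1.35 | 4.8% | 0.01 |

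Two hand calculations agree roughly with the table.
- *Uncorrelated rows.* The variance of the slope is inflated by about V = 1 + (m−1) × ICCx × ICCy, with m = 75. For the three rows V = 1 + 74 × 0.0025 = 1.185, 1 + 74 × 0.01 = 1.74, and 1 + 74 × 0.02 = 2.48. Rejection is about 2Φ(−1.96/√V), which gives 7.2%, 13.7% and 21.3%.
- *Correlated rows.* The expected slope is about r × √(ICCx × ICCy) × 20 × 19/20. That gives 0.5 × 0.05 × 20 × 0.95 = 0.475, then 0.5 × 0.10 × 20 × 0.95 = 0.95, then 0.5 × 0.1414 × 20 × 0.95 = 1.34.

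**Check 2: binary characteristic, countries of unequal size (30 to 200).** Prevalence varies between countries with SD 10 or 20 percentage points, and the outcome ICC runs from 0.01 to 0.10.
- *Uncorrelated.* Without country the test rejects in about 6% to 10% of runs at SD 10 points and about 6% to 20% at SD 20 points. A separate run of the same kind gave 5.5% to 22%. With country it rejects in 4% to 6%. At SD 20 points the coefficient stays centred on zero, but its spread is 1.34 without country and 1.15 with it at ICC 0.05, and 1.61 and 1.16 at ICC 0.10.
- *Correlated at 0.5.* Rejection is about 8% to 56%, with a mean shift of 0.4 to 2.4 points. By hand, with prevalence centred on 50%, the shift is r × SD of prevalence × √ICC × 20/0.25 × 0.95. The low end is 0.5 × 0.10 × 0.10 × 20/0.25 × 0.95 = 0.38. The high end is 0.5 × 0.20 × 0.316 × 20/0.25 × 0.95 = 2.40.

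**Check 3: switch outcome.** Assume a 40% switch rate and a combined country and site ICC of 0.10 to 0.20. The test rejects in 13% to 17% of runs at prevalence SD 20 points and 7% to 11% at SD 10 points, against about 5% to 6% with a country or site term. This used a linear-probability analogue of the logistic test, so it is indicative only.

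**Site alone.** With 15 patients per site and a site ICC of 0.01 to 0.10, the design effect 1 + 14 × ICC is 1.14 to 2.4. That is the upper limit, for a characteristic shared by a whole site.

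**The case against.** The strongest objection is that a separate, detailed SAP is announced, and handling of centre and country is ordinary SAP content. The predictor sentence says what will be considered and does not close the list, and the choice of model is tied to regression assumptions, of which independence is one. A reader might infer that the protocol excludes country and site. It does not say so, and their absence from the final models cannot be established from this document. What remains is that section 9.5.3 is not merely silent. It fixes pooling, two-variable regressions, stepwise selection and the kind of predictor. Even if the SAP added country as a candidate, the stepwise rule could drop it.

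A second objection is that uncorrelated country effects cause no systematic bias. That is right: in those runs the coefficient stays centred on zero, and the fault is a standard error that is too small. Bias needs correlated country effects, which the documents neither state nor rule out.

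Third, section 9.7 has secondary p-values read descriptively and asks for careful interpretation, and separate country analyses are planned. These temper the conclusions but do not adjust a pooled coefficient. Section 9.7 itself calls the country samples small, and its examples of confounders do not include country.

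Finally, a site random intercept in every univariate and subgroup model would be too rigid where data are sparse. That stands, and the fix allows for it.

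**Conclusion.** The point holds in conditional form. As written, the pooled models name no term for country or site, although the protocol accepts that practice and results may differ by country. Patient coefficients may therefore absorb between-country and between-site differences, and their standard errors may be too small.

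Under assumed country ICCs of 0.01 to 0.10, a characteristic with no within-country effect is flagged in about 6% to 22% of runs at a nominal 5%, against about 5% with country in the model. The low end is negligible. If country effects correlate at 0.5, the range is about 8% to 67% across the two sets of simulations, with a spurious coefficient of 0.5 to 1.3 TSQM points per SD of a continuous predictor, or 0.4 to 2.4 points for a binary one. All of this rests on ICCs and correlations that the protocol does not give.

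A reader might also infer that country effects are certain to distort these results, or that the stated half width of 1.01 is being disputed. Neither follows. The distortion needs variation by country in both predictor and outcome, and the precision of the primary mean is a separate matter.

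**What to change.** In section 9.5.3, state that the pooled full-population regression models, univariate and multivariable, include country as a forced term that is not subject to stepwise selection. State also that clustering by site is accounted for by a random intercept or cluster-robust standard errors, in particular in the model of planned DMARD switch. Allow country to be grouped by region, or entered as a random effect, in sparse subgroups and for sparse binary outcomes. If the SAP already provides this, a cross-reference from 9.5.3 is enough.

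Country and enrolling site should be known for every patient, so no new data are needed. The cost is a short addition to the text, slightly more analysis work, and wider intervals for characteristics that vary mainly between countries.
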